**Figure 1 F1:**
[figure not shown]
Participant flow diagram.

### Participant eligibility criteria

To be eligible for the study, an individual must be aged 15–30 years, with a diagnosis of mild to moderate depression, reside in Kamwokya, Naguru and Makerere areas in Kampala district, have a mobile phone, provide written informed consent and be able to speak Luganda or English.

Individuals aged 15–17 years must be either a mature minor or an emancipated minor (mature and emancipated minors are permitted to independently provide informed consent to participate in research).

Individuals who were mentally and or physically disabled as evidenced by a score inferior to 50% on the Karnofsky performance scale will be excluded from the study.

### Recruitment

Equal numbers of young people (15–30 years) living in the Naguru Go-down and Kamwokya slums in Kampala and students from Makerere University will be recruited and assessed for eligibility. A member of our team will be responsible for linking all excluded individuals to mental health services. Research assistants (RAs) will work with TMCG staff to launch an online and offline mental health awareness campaign to create awareness about mental health problems and available treatment options, including standard mental health services provided at government health facilities and the newly developed tele-psychotherapy service.

In the online mental health awareness campaign, given the high ownership of mobile phones in this demographic, more publicity will be done through SMS messaging and social media. The youthful population of university students will be reached through TMCG's social media channels, which are popular amongst young people, including University students, for example, the Facebook page has 58,000 followers.

This project will be explained in layman's language, and young people interested in participating will be invited to contact the study team.

In the offline mental health awareness campaign, the study team will work in collaboration with local leaders in Kamwokya and Naguru Go-down, as well as health workers at the Health facilities providing mental health services to conduct community sensitization meetings in which they will raise awareness about mental health problems and available treatment options including standard mental health services provided at government health facilities and the newly developed tele-psychotherapy service. Also, the project objectives will be explained in layman's language. About six to eight community meetings will be held, and at the end of each meeting, young people interested in participating in the project will be invited to contact the study team. This will ensure that all study participants are exposed to communication campaigns and then can be invited to participate.

### Randomization and masking

A biostatistician will randomly assign participants to either an intervention or control group using specialized statistical software, ensuring impartiality as the biostatistician has no direct contact with participants. Randomized blocks of varying sizes will be used to enhance the balance between study arms and reducing sequence predictability. Participants, each assigned a unique study code for anonymity, will be identified only by their phone number and study code to the research team. This randomization will be applied across three distinct communities—Naguru, Kamyokya, and Makerere University—with 100 participants from each being randomized, ensuring the study's findings can be generalized across different population subsets. Although participants will know if they are receiving the experimental or control intervention, the nature of these interventions will be masked from independent outcome assessors and data analysts to prevent assessment bias and ensure objective outcome evaluation.

### Study interventions

#### Tele-support psychotherapy model

The structure of the TSP model will be designed to align closely with the GSP model. Detailed content will be determined from the qualitative research we plan to undertake in the preparatory phase of the trial. Generally, the initial session will focus on establishing a safe therapeutic environment, clarifying expectations and setting ground rules. The second session will aim to increase the client's awareness of common mental health issues like depression, their symptoms, causes, and treatments, and the importance of addressing them to prevent complications. Sessions three and four will allow the client to express and share personal distressing experiences, provide emotional support, and equip them with skills to manage negative thoughts. The fifth session will be centred on teaching and practicing positive coping skills to manage difficult situations and excessive worries while avoiding negative coping mechanisms. In the sixth session, the focus will shift to coping with stigma and discrimination at personal, family, and community levels. The seventh session aims to empower clients with basic livelihood skills to identify income-generating activities, enhancing their ability to control their lives post-therapy. The final session involves the presentation of these income-generating activities by the clients, where they receive feedback and are guided in creating a realistic plan with a budget.

### The tele-psychotherapy call center

The tele-psychotherapy platform will be developed as an extension of The Medical Concierge Group (TMCG)'s existing tele-health services, also known as Rocket Health Africa. TMCG, a pioneering digital health entity, harnesses technology to offer a range of healthcare solutions including remote doctor consultations, community-based laboratory sample collection, doorstep pharmacy deliveries, and the creation of digital platforms for healthcare initiatives and research. For the prototype, the technical team will utilize detailed insights and schematic representations to craft the first version of the call platform. This will involve adapting the current infrastructure to introduce a mental health-specific toll-free line, ensuring community members can directly connect to the Rocket Health call center.

Upon dialing in, calls will be automatically redirected to available lay counselors, facilitating immediate start of the psychotherapy sessions. Following the initial setup, the developers will provide comprehensive orientation and training for the counselors involved in the project. These counselors, in turn, will educate their clients on navigating the call center access. Continuous enhancement of the call platform will be guided by user feedback, ensuring the service remains responsive to the needs of its clients.

### Standard mental health services (SMHS)

Standard mental health services provided at mental health treatment centers in Makerere University, Naguru, and Mulago, include a wide array of mental healthcare. However, mild to moderate mental health problems are addressed by mostly psychiatric clinical officers, nurses and counselors. Individuals seeking care will undergo physical and mental health assessments. Key services include unstructured counseling and or medication management for various mental disorders. For cases requiring specialized attention beyond the clinic's scope, referral systems ensure patients are directed to Butabika National Referral Mental Hospital.

### Sample size estimation

In a pilot trial the objective is not to prove superiority of the treatment but to test trial procedures and processes and to get estimates of parameters for the main trial sample size. According to Sim and Lewis et al, 2012, they propose a rule of the thumb for sample size of a pilot study which states that the sample size should be ≥55 and they do not put an upper limit (41). Other researchers argue that there is a trade-off, therefore, between having a small pilot study and a larger main trial or a larger pilot study and a smaller main trial. This is because the larger the pilot the more precisely estimated the variance will be and, hence, the smaller the inflation factor applied to the main study sample size calculation (42). For these reasons, we increased the sample size to 150 in each treatment arm.

### Study measures and data collection schedule

Study participants in the intervention and control arms will be asked to complete an interviewer-administered face-to-face or telephone-based standardized questionnaire to collect data on primary and secondary outcomes at baseline (T0), 6 months (T1), and 12 months (T2) after baseline.

### Sociodemographic variables

Sociodemographic variables will be assessed using a standardized socio-demographic questionnaire that will ask about descriptive information including age, gender, number of children, education, and relationship and employment status. Employment status will be categorized as “unemployed” and “employed”. Relationship status will be categorized as “never married”, “married/living with a partner”, and “divorced/separated”. Education status will be categorized as “secondary education”, “certificate”, and “diploma/degree”.

### Depression symptoms

Depression symptoms will be evaluated using the self-reporting questionnaire(SRQ-20) (43). Cross-cultural adaptation and validation of the SRQ-20 among PLWH in southern Uganda demonstrated that a cut-off score of six or higher provides optimal sensitivity (84%) and specificity (93%) for identifying current depression (44). This study will analyze SRQ scores as a continuous variable, and the scale's reliability will be assessed using Cronbach's alpha coefficient.

#### Suicide risk

The SAD PERSONS Scale (45) will be used in our study population because, despite its limitations and the lack of conclusive evidence for its predictive ability (46), it remains a widely recognized and practical tool for assessing suicide risk (47). Its simplicity and ease of use make it suitable for resource-limited settings where more sophisticated tools may not be readily available. Furthermore, incorporating it into the study will allow for the evaluation of its applicability and relevance in the African context, potentially contributing to the development of more tailored suicide risk assessment strategies in the future. Scores <4 will indicate low risk, 4–7 will indicate moderate risk, and ≥8 will indicate high risk, guiding intervention levels accordingly.

### Major depressive disorder

Major depressive disorder will be diagnosed using the MINI depression module, a structured diagnostic interview developed for the Diagnostic and Statistical Manual of Mental Disorders (4th Edition) (48).The psychometric properties of the MINI have not been formally evaluated in Uganda. However, the depression diagnostic section has been translated into Luganda, culturally adapted, and previously utilized in this context (49). The module will include two screening questions about depressed mood and loss of interest in daily activities over the past four weeks, seven additional questions about depression symptoms, and one question on functional impairment. A diagnosis will be made if the participant positively answers five or more symptom-related questions and the functional impairment question over a four-week period.

#### Anxiety symptoms

Anxiety symptoms will be assessed using the GAD-7 questionnaire (50). Although the GAD-7 has been validated in other African contexts (51, 52), it has not yet been validated in Uganda. This study will evaluate its reliability using Cronbach's alpha to determine its applicability in the study population. GAD-7 scores will be analyzed as a continuous variable within the study sample.

#### Alcohol use

Alcohol use will be assessed using the 3-item AUDIT-C, a shorter version of the AUDIT (53). The 3-item AUDIT-C, a shorter version of the Alcohol Use Disorders Identification Test(AUDIT), has not been validated in Uganda but evaluated and validated in several African contexts (54, 55). This tool will be used to assess risky alcohol use. Each question will be rated on a four-point scale, with total scores ranging from 0 to 12. A score of 4 or higher in men or 3 or higher in women will be recommended as an indicator of hazardous drinking behavior. The variable will be reported both categorically, using these cut-off points, and continuously, using total AUDIT-C scores.

#### Self-esteem

Self-esteem will be measured using the 10-item Rosenberg Self-Esteem Scale (56), with scores ranging from 10 to 40, where higher scores indicate higher self-esteem. The scale has not been validated in Uganda but has been evaluated and validated in several African contexts (57, 58). The scale's reliability will be assessed using Cronbach's alpha, and scores will be modelled as a continuous variable.

#### Disability days

Disability days will be assessed by asking: “How many working days have you lost due to depression-related symptoms in the previous 30 days?” Disability days reported will be modelled as a continuous variable. Single-item measures have shown good reliability and validity in assessing general health and physical activity (59).

#### Social support

Perceived social support will be assessed with the 12-item multidimensional social support scale (60). Perceived social support will be measured using the 12-item Multidimensional Scale of Perceived Social Support (MSPSS). This scale has been validated in Uganda, and its three-subscale structure—assessing support from family, friends, and significant others—has been confirmed (61). The scale uses a seven-point Likert format, with higher scores reflecting greater perceived support. Total scores will be calculated and analyzed as a continuous variable. The scale's reliability will be assessed using Cronbach's alpha for this study population.

#### Stigma

Stigma will be assessed using Nyblade and MacQuarrie's method, involving perceived, experienced, and internalized stigma (62) The tool is part of a broader effort to develop programmatic knowledge and interventions aimed at reducing stigma associated with various health conditions such as HIV, mental illness, and substance abuse. This tool is informed by a systematic review of literature and aims to fill existing gaps in stigma reduction strategies, particularly in health facilities. Scores will range from 0 (no stigma) to 40, with higher scores indicating higher levels of stigma. Scores will be modelled as a continuous variable.

#### Therapeutic alliance

The Scale to Assess the Therapeutic Relationships–Patient Version (STAR-P) will be used to evaluate the quality of therapeutic relationships from the patient's perspective, particularly in community mental health settings (63). It consists of 12 items divided into three subscales: positive collaboration, positive clinician input, and non-supportive clinician input. While not validated in Uganda, the STAR-P has been adapted into various languages for cultural relevance (64, 65) and has demonstrated strong psychometric properties, including good test-retest reliability (*r* = 0.76) and internal consistency, with high Cronbach's alpha values across diverse populations (66). The scale's reliability will be assessed using Cronbach's alpha for this study population.

#### Feasibility

Indicators of feasibility will be assessed by determining the proportion of eligible participants who engage in either intervention (reach), the proportion who attend all 8 sessions of either intervention (dose delivered), and the proportion lost to follow-up (attrition), using data from attendance registers.

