In the trial phase, we shall conduct a pilot single-blinded randomized controlled trial to test the feasibility and

acceptability of using TSP in combination with standard mental health services(SMHS) vs. SMHS only to treat mild to moderate depression among youth in Kampala district. We aim to randomize 300 youth (1:1) to either both TSP and SMHS (*N* = 150) or SMHS only (*N* = 150). The 150 subjects in each arm will be recruited from three communities (Makerere University (*N* = 50), Kamwokya slums (*N* = 50) and Naguru go-down slums (*N* = 50) in each treatment arm and invited to participate. Participants will be evaluated at baseline, 6 and 12 months after baseline assessment.

A longitudinal process evaluation of the delivery of TSP using mobile phones and SMHS using mixed methods will run alongside the trial to assess acceptability, feasibility, fidelity, barriers and facilitators and how intervention recipients respond to the different intervention components. Open-ended exit interviews with recruited trained lay counsellors and study participants will seek to understand stressors in their communities, their own psychosocial support needs, and their knowledge regarding mental health after training, satisfaction, barriers and facilitators of participation in TSP sessions. Attendance registers and training logs will be used to track indicators of feasibility.

The study protocol is registered in the Pan African Clinical Trials Registry. The reporting of the trial will be in accordance with the Standard Protocol Items: Recommendations for Interventional Trials (SPIRIT) guidelines (39) for intervention trials (see Supplementary File S1) and the CONSORT statements for pilot randomized trials (40). The study was submitted to and approved by both the Makerere University College of Health Sciences Research Ethics Committee and the Uganda National Council of Science and Technology. All study participants will be required to provide written informed consent. Participants will receive a financial incentive to compensate for their time and defray internet data costs (if any). Figure 1 summarizes the trial profile.

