### Retention

To enhance adherence to the intervention sessions and maintain participant retention, lay health workers (LHWs) conducting the TSP sessions will receive a financial reward for their dedication to the project. Additionally, to re-engage participants who miss their TSP sessions, LHWs will be provided with airtime allowances to facilitate direct follow-up calls.

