### Statistical analyses

The process evaluation of this pilot trial will adopt a mixed methods approach to thoroughly assess its primary outcomes, which include feasibility, acceptability, fidelity, the mediating processes behind observed effects, and the contextual factors acting as barriers or facilitators. For qualitative insights, accuracy checks will be performed on transcripts from Focus Group Discussions (FGDs) and Key Informant (KI) interviews, followed by translation into English and transcription. To ensure confidentiality, all interview data and notes will be anonymized and securely stored in the project's cloud-based folders. The qualitative data analysis will be conducted using MAXQDA Analytics Pro 2022 (Release 22.5.0), employing a grounded inductive approach to unearth recurring patterns and themes within the data. To enhance the analysis’ credibility, the thematic analysis will be collaboratively undertaken by at least three research team members. This collective effort aims to facilitate rich discussions, leading to a consensus on the emerging coding themes and a deeper understanding of the findings.

The interview data will initially be coded according to some themes corresponding to the focus questions. The codes will be used to construct matrix displays based on the co-occurrence of codes and the two treatment groups. The resulting matrix display will provide both the frequency and detailed content of responses, allowing us to assess how often responses varied between the two treatment groups. Inter-coder reliability will be assessed.

For the quantitative data, we will do bivariate analyses with *χ*^2^ tests and independent two-sample t tests to compare baseline demographic and psychosocial variables between study groups. Similarly, we will also do bivariate analyses to compare these variables between those who had completed all sessions (completers) and those who had not (non-completers).

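### A primary feasibility indicator, attendance at all eight sessions, rests on attendance registers alone, while those who deliver TSP are rewarded with the aim of raising adherence; TSP entries should be checked against call-platform records

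*Protocol article*

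**What the plan says.** The Statistical analyses section of the protocol article lists the "primary outcomes, which include feasibility, acceptability, fidelity" of the process evaluation, so feasibility is a primary outcome. The Feasibility section names three indicators: reach, dose delivered and attrition. Dose delivered is "the proportion who attend all 8 sessions of either intervention (dose delivered", and the indicators are obtained "using data from attendance registers". The Study design section gives the source a second time: "Attendance registers and training logs will be used to track indicators of feasibility".

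The Introduction says that TSP is offered individually by mobile phone. On the delivery channel, the call center section says: "Upon dialing in, calls will be automatically redirected to available lay counselors, facilitating immediate start of the psychotherapy sessions". SMHS is provided at treatment centers (Standard mental health services; Trial status).

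The Retention section begins with its purpose, "To enhance adherence to the intervention sessions and maintain participant retention", and continues that "lay health workers (LHWs) conducting the TSP sessions will receive a financial reward for their dedication to the project". It also gives these workers airtime to telephone participants who miss sessions.

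**The concern.** In a one-to-one telephone session there is normally no third person to see whether it took place or how long it lasted. The only named source for the indicator is a register. The people delivering the sessions receive a reward directed at adherence, which is the quantity that dose delivered measures. The article describes no check of the register against anything else. The fidelity assessment is a questionnaire completed by supervisors, and it is not described as an attendance audit.

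Two uses of the figure are exposed. First, the Introduction hypothesizes better feasibility for TSP than for control. The reward is described for one arm only, so any over-recording that it prompted would favor TSP in that comparison. Second, the Statistical analyses section compares completers with non-completers, and over-recording would place some non-completers in the wrong group. A larger sample would cure neither problem.

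**Working it through.** **What the texts establish**

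| Link in the argument | Stated? | Where |
|---|---|---|
| Feasibility is a primary outcome | Yes | Statistical analyses |
| All-eight attendance comes from registers | Yes, source given twice | Feasibility; Study design |
| TSP deliverers are rewarded, with adherence as the aim | Yes | Retention |
| TSP deliverers keep the registers | No | – |
| Reward depends on recorded attendance | No; it is for dedication | Retention |
| TSP calls are routed through a platform | Yes, for calls dialed in | Call center section |
| Platform records are a source or check for attendance | Not named | – |

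**Size.** The article gives no expected completion rate, feasibility threshold or register error rate, so there is no figure of its own to reproduce. The inputs from the article are 154 participants assigned to TSP plus SMHS (Trial status) and 8 sessions. All other inputs below are assumptions.

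*Sampling error.* With 60% true completion: 1.96 × √(0.60 × 0.40 / 154) = 0.077, or 7.7 points. For proportions from 50% to 80% the half-width runs from 7.9 down to 6.3 points.

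*Model 1: whole participants misrecorded.* Let g be the share of true non-completers entered as complete. Reported proportion = 0.60 + g × 0.40.
- g = 0.10: 0.60 + 0.04 = 0.64, which is 4 points too high.
- g = 0.25: 0.60 + 0.10 = 0.70, which is 10 points too high.
- The bias equals the half-width at g = 0.077 / 0.40 = 0.19, about one non-completer in five.

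*Model 2: single sessions misrecorded.* Let a be true attendance per session, with sessions independent, and f the share of missed sessions entered as attended. True completion = a^8. Registered completion = (a + (1 − a)f)^8.

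| a | True | f = 0.10 | f = 0.20 | f = 0.30 |
|---|---|---|---|---|
| 0.85 | 27.2% | 31.3% | 36.0% | 41.2% |
| 0.90 | 43.0% | 47.0% | 51.3% | 56.0% |
| 0.95 | 66.3% | 69.2% | 72.1% | 75.2% |

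The overstatement runs from 2.8 points (a = 0.95, f = 0.10) to 13.9 points (a = 0.85, f = 0.30).

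Under both models the milder error rates give a bias below the sampling half-width and the heavier ones exceed it. This shows possible size only and is no evidence that misrecording happens.

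**The case against.** The strongest reply is that the route to bias needs two facts that the article does not state: that the rewarded workers complete the registers, and that the reward rises with recorded attendance. If either is untrue, the route weakens or closes. Who fills in a register and how staff are paid are details that a condensed article may leave to the full protocol. A reward may also raise attendance genuinely, which is not measurement error. This stands, and it limits the point to an unguarded risk. It does not remove the point, because the choice of source is stated and a check is close at hand.

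A reader might also infer that every session passes through the platform, so that its records could simply replace the register. The article does not support that. SMHS is given at treatment centers, and the airtime-funded follow-up calls may bypass the platform. Replacement would make the source differ by arm. It could also undercount TSP where calls drop, which is plausible given the inconsistent network access that the Discussion acknowledges.

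Nor does the article support saying that the register cannot tell a full session from a short re-engagement call, because the register's content is not described. Registers can also omit sessions, and under an all-eight rule one omission turns a completer into a non-completer. The net direction of error is therefore unknown.

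Some outside view of delivery exists: professional counselors supervise the lay counselors, supervisors report on delivery, and participants have exit interviews. None of these is described as verifying attendance session by session.

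**Conclusion.** The point holds as an inexpensive improvement to how a primary indicator is measured. The article fixes registers, with training logs, as the source, and describes an adherence-directed reward for those who deliver TSP and no comparable one for SMHS staff. It names no cross-check, although TSP calls are routed through a platform.

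It would go too far to conclude that the completion figure is inflated or that paid counselors are recording their own results, since the article says neither. The size is unknown. The 4 to 10 points, against a half-width of about 7.7 points for 154 participants at 60%, rest wholly on assumed completion and misrecording rates. The remedy rests on one further assumption, that the platform retains usable call records.

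**What to change.** For TSP only:

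- Keep the attendance register as the source used in both arms.
- Check each registered TSP session against the platform record, matched on phone number or study code, date and call duration. The Randomization and masking section says that participants are identified by phone number and study code, so a linking key exists.
- Report the agreement between register and log. Give the all-eight proportion twice, as registered and as log-supported.
- Flag off-platform and dropped calls, and do not discount them automatically.
- Repeat the completer versus non-completer comparison with log-supported completion as a sensitivity analysis.

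The cost is a data export and a match, with no new participant contact. Recruitment is complete according to the Trial status section, so the check depends on the records having been retained. The sponsor should accept that the log-supported completion figure may be lower than the registered one.

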Further, we will determine whether TSP using mobile phones can be delivered by lay counselors as planned and also explore causal and contextual factors (barriers and facilitators) influencing access to TSP. Secondary objectives will include an exploration of the preliminary effectiveness and cost-effectiveness of tele-support psychotherapy using mobile phones in treating mild to moderate depression among youth. Further, we will explore mediators and moderators of the effect of TSP on depression. We hypothesize that compared to the control intervention, TSP using mobile phones will demonstrate better feasibility, acceptability, preliminary effectiveness, and cost-effectiveness. The primary endpoint will be six months from baseline. The data obtained will be used to design a definitive trial which will test the hypothesis that TSP added to SMHS leads to more reduction in depression symptoms than the sole use of SMHS among youth in Kampala district.

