#### Acceptability

The following indicators of acceptability including participant satisfaction, TSP counselor knowledge and attitudes, and the perceived effectiveness of the intervention in reducing depression will be evaluated using a 9-item questionnaire (67).

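### Two of the six primary feasibility and acceptability indicators have no counterpart in the control arm, so the hypothesis that TSP is better cannot be tested fairly on them

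*Protocol article*

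**What the plan says.** The abstract of the protocol article names feasibility and acceptability as primary outcomes. The Introduction then states a comparative hypothesis on them: "We hypothesize that compared to the control intervention, TSP using mobile phones will demonstrate better feasibility, acceptability, preliminary effectiveness, and cost-effectiveness". Sample size estimation says that in a pilot "the objective is not to prove superiority of the treatment".

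The Feasibility section gives three indicators: reach; dose, which is "the proportion who attend all 8 sessions of either intervention (dose delivered"); and "the proportion lost to follow-up (attrition), using data from attendance registers". The Acceptability section gives three more: "participant satisfaction, TSP counselor knowledge and attitudes", and perceived effectiveness.

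The control condition is set out under Standard mental health services (SMHS): "Key services include unstructured counseling and or medication management for various mental disorders". No number of sessions is given. The eight-session sequence appears only for TSP, in the description of the TSP model and in the Discussion. Under Trial status, 154 participants were allocated to TSP with SMHS and 146 to SMHS only; the latter were told to attend the nearest treatment centre.

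Statistical analyses plans a comparison between "those who had completed all sessions (completers) and those who had not (non-completers"), without saying whether the arms are pooled. It also describes "primary outcomes, which include feasibility, acceptability, fidelity, the mediating processes behind observed effects", whereas the Introduction puts mediators among the secondary objectives.

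**The concern.** An indicator can support a between-arm hypothesis only if it has a meaning in both arms. Attending all eight sessions is a property of the TSP course. Applied to SMHS, it is either undefined or close to zero whatever the quality of the control service. Any uptake of the TSP course would then look like better feasibility, even a completion rate low enough to tell the sponsor that the course cannot be delivered. The counsellor item has the same defect, because controls receive no TSP.

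A second problem concerns attrition. The definitive trial needs to know what proportion of randomised participants will provide the outcome at follow-up. A register of attendance at sessions answers a different question: a participant can stop attending and still be assessed, or attend and then not be assessed. Retention also provides for follow-up calls to participants who miss TSP sessions and describes no SMHS equivalent, so attendance records are unlikely to be like for like between arms.

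**Working it through.** **The plan's own figure.** The sample size of 150 per arm rests on a rule of thumb (at least 55) and a precision argument, with no alpha, power or rate, so it cannot be reproduced. The totals agree: 2 × 150 = 300, and 3 sites × 50 × 2 arms = 300. The point here is about outcome definition, so the indicators were checked one at a time.

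**Which indicators exist in both arms?**

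| Indicator | TSP arm | SMHS arm |
|---|---|---|
| Reach | yes | yes, but a clinic visit instead of a phone call |
| Dose: all 8 sessions | yes | no eight-session course described |
| Attrition | yes | yes |
| Participant satisfaction | yes | yes |
| TSP counsellor knowledge and attitudes | yes | no TSP counsellor |
| Perceived effectiveness | yes | yes |

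Two of six have no SMHS counterpart; four can be measured in both arms.

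**What the dose indicator would do if compared.** Assume a control rate of 0% and a two-sided 5% level; neither is in the documents. By Fisher's exact test, the smallest number of TSP completers that gives p < 0.05 is:

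- planned arms: 6/150 (4.0%) against 0/150, p = 0.030;
- arms as randomised: 6/154 (3.9%) against 0/146, p = 0.030.

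On that assumption, 148 of 154 TSP participants could fail to complete the course and the indicator would still read as a nominally significant advantage.

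**What the TSP arm alone can give.** The 95% half-width is 1.96 × √(p(1 − p)/n) with n = 154:

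- p = 0.70: 1.96 × √(0.21/154) = 0.072, or 7.2 points;
- p = 0.80: 1.96 × √(0.16/154) = 0.063, or 6.3 points.

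The rates are illustrative. This precision is useful for planning a larger trial, and no control arm is needed for it.

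**The completer comparison, if pooled over arms.** If no control counts as a completer, 146/300 = 48.7% of the sample are non-completers by allocation. With an assumed TSP completion of 70% there are about 108 completers, all in TSP, and 46 + 146 = 192 non-completers, of whom 146/192 = 76% are controls. At 80% the figures are about 123 completers and 31 + 146 = 177 non-completers, 146/177 = 82% controls. The comparison would then be largely one of arm against arm.

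**Attrition.** The Feasibility section ties loss to follow-up to attendance registers. Study measures and data collection schedule places outcome collection at baseline, 6 months and 12 months in both arms. The follow-up that can be lost is therefore the 6- or 12-month assessment.

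**The case against.** The best defence is that no formal comparison is planned. Statistical analyses gives between-arm modelling only for the secondary outcomes; the Introduction also words the primary objective as evaluating the feasibility and acceptability of TSP itself; and Sample size estimation disclaims superiority. The comparison of coded responses between treatment groups concerns interview data. This stands in part: the comparison rests on the hypothesis, not on a specified test. But the hypothesis is an affirmative statement about the primary outcomes, the dose indicator is expressly worded for both interventions, and the disclaimer of superiority contradicts the hypothesis and leaves the dose definition as it is.

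A reader might go further and infer that the feasibility and acceptability indicators as a whole do not exist under SMHS, so that a favourable result is guaranteed. The documents do not support that. Reach, attrition, satisfaction and perceived effectiveness can all be measured in controls; primary-outcome data are collected in both arms, and Study design extends the process evaluation to SMHS. Reach can be split by arm, since everyone randomised is eligible. Attrition taken from registers has a doubtful source but does not favour TSP by definition.

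Three further limits are fair. The 0% control rate is an assumption: the article leaves the SMHS dose undefined and does not show it to be zero. Pooling in the completer analysis is one reading of a sentence that could be meant for TSP alone. The article does not say what the registers contain, so it is not established that attrition would be mismeasured. Nor is the absence of progression thresholds a fault in an article that may leave them to a fuller document.

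**Conclusion.** The point holds for two of six primary indicators. The eight-session dose and the TSP-counsellor item have no SMHS counterpart, so better feasibility and acceptability cannot be tested fairly on them, and dose favours TSP by construction. Under an assumed 0% control rate, about 4% completion in TSP would reach nominal significance. The hypothesis in the Introduction also conflicts with the stated purpose of the pilot under Sample size estimation.

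Two related wordings need correction: the source named for attrition, and a completer comparison that, if pooled, would put most or all of the 146 controls among the non-completers. The status of mediation, primary in one section and secondary in another, is a smaller inconsistency. None of this prevents the trial from answering its feasibility question, because the TSP-arm estimates are informative in their own right. A fuller protocol or analysis plan may define SMHS versions of these indicators, but it would have to depart from the present text to do so.

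**What to change.** 1. In the Introduction, remove feasibility and acceptability from the comparative hypothesis, or limit it to indicators defined in both arms, and reconcile it with Sample size estimation.
2. Estimate the eight-session dose and the TSP-counsellor indicator in the TSP arm only, with 95% confidence intervals.
3. Define attrition in each arm as participants with no 6-month assessment, and separately no 12-month assessment, divided by the number randomised.
4. Report reach, satisfaction and perceived effectiveness in both arms, noting that a phone call and a clinic visit are not like for like.
5. Restrict the completer analysis to the TSP arm.
6. Make Statistical analyses and the Introduction agree on whether mediation is primary or exploratory.

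The cost is mainly wording. Attrition so defined needs only a record of who completed the scheduled assessments. The sponsor gives up the claim of better feasibility. Trial status reports only baseline analysis under way, and data analysts are to be masked, so the changes should be dated and made before allocation is revealed to the analysts.
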